## Results

3

### Quantitative analyses

3.1

Data-analyses will be carried out by using the latest version of R and Rstudio. Analyses will be done on an intention-to-treat basis. Frequencies and percentages will be given for gender, co-morbid disorders, trauma type (sexual/physical abuse <12 years, sexual/physical abuse during adolescence (>12 - <18), sexual/physical abuse adulthood, other trauma), treatment history (types of previous treatment) and drop-out. Means, standard deviations, range and medians will be calculated for age, number of different traumata experienced in life and treatment history in years. To test for selection bias, independent two-sided t-tests will be done comparing the data of the study sample with regular ROM measurements (CAPS-5, PCL-5, SDQ-20 and DES) of non-participants at T0a. For this purpose, a total sample of N=128 (N=64 in each group) is needed with a power of.80 and an alpha of.05.

#### Short and long term effects of DBT-PTSD

3.1.1

To study short-term within-subjects differences, change scores will be calculated with the first three time points (T2-T1=Δtreatment and T1- T0=Δwaiting-list), resulting in four Δ-variables for PTSD, six for dissociation, two for NNSI and suicidal ideation and two for borderline symptomatology. Two-sided paired-samples t-tests will be conducted to compare the Δtreatment and Δwaiting-list scores. We use two-sided tests to maintain a conservative α level. When the anticipated waiting list period turns out to be less than three months, we will consider excluding the participant from the paired t-test analyses. When, at the end of the study, the waiting list period appears to vary much more than expected, and we might need to exclude too many patients, we will consider alternative statistical analyses that are able to deal with this variability, such as linear mixed model analysis. *Post-hoc* analyses to assess long term treatment effects in PTSD, dissociation, NNSI and suicidal ideation, and borderline symptomatology will be carried out with linear mixed model analyses with time as random effects. We will include two predictors of treatment effects on PTSD severity, as measured with the CAPS-5 and PCL-5 into the PTSD model: 1) baseline severity of BPD symptoms (using the total score on the BPDSI) and 2) cluster C personality disorders (with the sum of the dimensional SCID-5-P scores of the three cluster C personality disorders). Further, we will use linear mixed model analyses to study the effects of DBT-PTSD on social functioning and quality of life over time.

#### Symptom trajectories with diary data

3.1.2

Finally, as more explorative objectives, we intend to study symptom trajectories on a group and individual level with the diary data. We will use linear mixed model analyses and graphs to show symptom trajectories over time with PTSD intrusive symptoms, emotion dysregulation behaviors (non-suicidal self-injury, high risk behavior, binge eating or self-induced vomiting, alcohol use, drugs/medication use, anger, other problem behavior), suicidality, hours of sleep, happiness and undertaking pleasant activities. Linear mixed model analyses are capable of handling missing data, even when a substantial part of the data is missing. We hypothesize that when PTSD symptoms decrease, improvements on the other variables will follow. To test this hypothesis, we will include PTSD symptoms as a time-varying covariate with a two week lag in our linear mixed models.

Second, we study the degree to which clients invest in their treatment, operationalized by the DBT-PTSD diary items: ‘time spent on therapeutic assignments’ (in minutes) and ‘exposure assignments carried out’ (yes/no), as predictors of treatment outcome. We will use the CAPS-5 and PTSD symptoms of the diary to measure change in PTSD symptoms and the diaries emotion dysregulation behavior items for emotion dysregulation. We hypothesize that clients who are motivated and invest in their treatment, by doing more exposure assignments and spending more time on therapeutic assignments, will benefit more from DBT-PTSD. To test this hypothesis, we will split the sample in half to compare clients with the highest and lowest scores on homework and exposure assignments during the first four weeks and over the whole course of treatment. We will again use linear mixed model analyses with a time x group interaction in our model.

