### Procedure

2.2

Clients eligible for DBT-PTSD are first informed about the study during the commitment interview. The importance of truly committing to the treatment is then discussed and afterwards clients committed to DBT-PTSD are then placed on the waiting list. Those interested in study participation are sent detailed written information and receive a follow-up telephone call to provide further information. Clients are informed that study participation entails extra questionnaires and interviews, beside the standard diagnostic procedures and Routine Outcome Measurements (ROM).

During the baseline assessment (T0), informed consent is obtained by the research nurse. Interviews are performed by independent research assistants and clinical psychologists (in training). The interviewers are trained in the use of the instruments and regularly attend group intervision meetings to enhance reliability. Clients complete self-report questionnaires online. To improve study participation and retention clients can choose between being interviewed at the mental healthcare facility of via video call, This is particularly convenient for those living far away from the treatment center. We also approach clients enrolled in the TTS who finished DBT-PTSD in the previous two years and invite them for a qualitative interview about their experiences. These interviews are conducted by two clinical psychologists in training (AK and PV) who are unacquainted with these clients. Clients give an additional informed consent before starting this interview. Finally, we use the DBT-PTSD diary data from clients that started DBT-PTSD between 2019 (when the diary was digitalized) and December 2023 to study symptom trajectories. Clients fill in this daily diary as part of the treatment program.

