### DBT-PTSD

2.5

This inpatient, modular DBT-PTSD treatment program of 12 weeks largely follows the original protocol developed by Bohus and colleagues (28, 29). **Table 1** provides an overview of all treatment modalities. Protocol modifications include the addition of four exposure sessions (total 16) and systemic therapy. In general, the treatment consists of three phases and has both fixed and optional modules. In phase 1 (weeks 1 - 2) clients identify values they find important in life and goals they wish to work on during and after finishing the treatment. They also learn to recognize their avoidance mechanisms, determine their index trauma and acquire DBT skills. Trauma-focused therapy is the main focus of phase 2 (weeks 3 - 10). The individual psychotherapy consists primarily of PE, but has elements of cognitive therapy as well. Also, therapists can, after consultation with their client and the treatment team, use EMDR when that seems appropriate. In the third phase (weeks 11-12) the objective is to help clients accept trauma-related elements of their personal history and focus on how they wish to pick-up their daily lives after finishing treatment. Enhancing self-acceptance and self-compassion are integrated throughout the treatment program.

**Table 1 T1:** Overview of modules within clinical DBT-PTSD across the three phases of treatment.

Individual		Group	
Trauma-focused therapy^123^ᵐ Exposure *in vivo* ^23^* Mentor meetings^123^ DBT Diary review^123^ Psychomotor therapy^23^* Systemic therapy^123^*ᵐ	Creative therapy^23^ Nightmare training^23^* Mindfulness^123^ Expert by experience session^123^*ᵐ	Skills training^123^ Psycho-education^12^ Self-worth^23^* Interpersonal effectiveness^23^* Creative therapy^123^*	Psychomotor therapy¹²³ Conquering life³ Mindfulness ¹²³ Sports modules¹²³ᵐ Self-defence^¹²³^

Treatment phase = ¹²³; Optional modules = *; Protocol modifications = ᵐ.

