#### Client perspectives and individual symptom trajectories

2.6.6

With a qualitative semi-structured interview, we study clients’ experiences with DBT-PTSD. With open questions clients are asked about subjects like, changes they experienced during and after treatment, factors they perceived as helping or hindering the treatment process and their suggestions for improvement. Interviews will take 60 to 90 minutes and will be audiotaped and afterwards verbatim transcribed.

We use the DBT-PTSD diary to assess symptom trajectories and the individual differences herein between clients. The DBT diary was developed and provided by Bohus and colleagues in the Central Institute for Mental Health in Mannheim, Germany. As part of treatment, clients keep a digital daily diary during the twelve weeks of treatment. Items in this diary include among others, PTSD intrusions, sleep, suicidality, problem behavior, happiness, time spent on therapeutic assignments and frequency of exposure assignments. Items vary from nominal, (yes/no), ordinal (5-point Likert scale) to continuous.

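### The diary test of whether other symptoms improve after PTSD runs in one direction only, so it can confirm that order when symptoms merely move together

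*Protocol article*

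**What the plan says.** Section 3.1.2 (Symptom trajectories with diary data) introduces this work as exploratory: "Finally, as more explorative objectives, we intend to study symptom trajectories on a group and individual level with the diary data". It nevertheless states a directional hypothesis, "We hypothesize that when PTSD symptoms decrease, improvements on the other variables will follow", and ties a specific test to it: "To test this hypothesis, we will include PTSD symptoms as a time-varying covariate with a two week lag in our linear mixed models". The other variables are emotion dysregulation behaviours, suicidality, sleep, happiness and pleasant activities.

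Section 2.6.6 gives the data: "clients keep a digital daily diary during the twelve weeks of treatment". Section 2.2 gives the sample: "we use the DBT-PTSD diary data from clients that started DBT-PTSD between 2019 (when the diary was digitalized) and December 2023". The number of clients with diary data is not stated.

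The section names no model in which earlier values of the other variables predict later PTSD symptoms, and no term for the outcome's own earlier value. It does not rule either out.

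**The concern.** A claim that one thing follows another needs evidence against two rivals: that both change together, and that the order is reversed. A lagged PTSD covariate on its own excludes neither. Symptoms carry over from week to week, so PTSD two weeks ago is related to the outcome two weeks ago, and through that to the outcome now. The coefficient can be clearly positive with no lead in either direction.

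The reverse order is a fair rival here. According to section 2.5, in weeks 1-2 clients "determine their index trauma and acquire DBT skills", and trauma-focused work becomes the main emphasis in weeks 3-10.

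At stake is a statement that improvement in self-injury, suicidality or sleep came after PTSD relief, when the diary might show only parallel change. Section 4.2 hopes the trajectories will help clinicians adjust treatment sooner, so the order matters to the intended reader.

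**Working it through.** **Inputs.** From the article: a daily diary over 12 weeks, a two-week lag and a linear mixed model. The article gives no sample size, power or error rate for this analysis, so there is no figure to reproduce. Assumed: 56 clients (the study total in section 2.8; the diary sample may differ), 12 weekly scores, and all variables scored so that higher is worse. Persistence, correlation, trend and measurement error are also assumptions.

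**Step 1: algebra.** Let P (PTSD) and Y (outcome) each have week-to-week persistence φ and same-week shocks correlated ρ, with no effect of either on the other. Then Y(t) = φ²·Y(t−2) + shocks after t−2, and the same-week correlation of P and Y is ρ. Hence

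corr[P(t−2), Y(t)] = φ²·ρ.

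With ρ = 0.6:
- φ = 0.4: 0.16 × 0.6 = 0.096
- φ = 0.6: 0.36 × 0.6 = 0.216
- φ = 0.8: 0.64 × 0.6 = 0.384

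By symmetry the reverse correlation is the same. Once Y(t−2) is in the model, P(t−2) adds nothing, because the later shocks are unrelated to it. If Y(t−2) is measured with error, that protection is only partial.

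**Step 2: fitted models, no lead in either direction** (100 trials per row, ρ = 0.6 except in the first row, where the series are independent). Entries are the percentage of trials with a positive lag coefficient at two-sided p<.05, with p<.01 in brackets. The nominal values in this direction are 2.5 (0.5).

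| Setting | PTSD lag, random intercept | plus random time slope | random intercept plus own lag | Reverse, random intercept |
|---|---|---|---|---|
| Independent series, φ 0.6 | 3 (0) | 3 (0) | 1 (0) | 5 (1) |
| φ 0.4 | 17 (8) | 6 (1) | 5 (3) | 19 (13) |
| φ 0.6 | 73 (58) | 13 (5) | 4 (1) | 69 (46) |
| φ 0.8 | 99 (90) | 46 (25) | 3 (1) | 98 (93) |
| φ 0.6, trend | 83 (66) | 22 (11) | 11 (6) | 79 (70) |
| φ 0.8, trend | 97 (97) | 46 (30) | 3 (3) | 98 (98) |
| φ 0.8, trend, measurement error | 98 (88) | 49 (30) | 43 (27) | 95 (90) |

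The Monte Carlo standard error is √(p(1−p)/100): 4.4 points at 73% and 1.6 points at 2.5%. The reverse model is positive about as often as the forward one, so fitting both would expose the ambiguity.

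**Step 3: other specifications.** These runs make different assumptions about client-level variation and are not pooled with the table. All rates are at p<.05.
- φ 0.8, ρ 0.36, 200 trials: random intercept 58%, random slope 16%, random intercept with AR(1) residuals 3%, own lag 1%.
- φ 0.8, ρ 0.6, 200 trials: 87%, 21%, 3% and 0.5% in the same order.
- φ 0.4, ρ 0.36: random intercept alone 2.5%.
- φ 0.8, ρ 0.6 with measurement error: AR(1) residuals 42%, own lag 18%.
- φ 0.8, ρ 0.36, 150 trials: uncentred PTSD 65%, PTSD centred within clients 57%, own lag 4%. Centring is therefore not the cure. When PTSD truly led, all of these models detected it in 100% of trials.

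**The case against.** The strongest reply is that the article fixes only the predictor and the model class. Random effects and residual covariance are details an article may leave to the analysis plan, and they decide the error rate. AR(1) residuals, a routine choice for serial data, bring false confirmation to about 3% when there is no measurement error. Section 3.1.1 treats time as a random effect in the long-term models, which hints at a random slope here too. Much of this stands: no single rate can be called the behaviour of the planned model, and it is wrong to say that the test *will* confirm the hypothesis. It does not dispose of the point. With measurement error, AR(1) residuals still gave 42%, and none of these choices examines the reverse order.

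Three stronger readings are tempting and not supported:
- *That skills gains come first by design.* Table 1 marks both skills training and trauma-focused therapy in all three phases, so the sequence is one of emphasis only.
- *That losing weeks 1-2 as outcome days is a separate flaw.* Any two-week lag does this (12 × 7 = 84 days, less 14, leaves 70), and the fix below keeps that lag.
- *That the study intends a claim of mechanism.* The hypothesis says that improvements follow, not that PTSD relief causes them.

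Section 3.1.2 also plans graphs of each variable over time, which would help to show what moved first.

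**Conclusion.** The point holds in limited form. The stated test runs in one direction and names no outcome lag, so it cannot by itself separate PTSD leading from parallel change. Under assumed values, false confirmation runs from about the nominal 2.5% (low persistence, or AR(1) residuals without measurement error) to over 90% (high persistence with a random intercept only). Where the real diary data would fall in that range cannot be known from the article. The spurious coefficient comes from the model and not from sampling noise, so a larger diary sample would not remove it. The analysis is exploratory and no primary result depends on it: minor priority.

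**What to change.** In section 3.1.2, for each outcome:
1. Fit both directions: PTSD two weeks earlier predicting the outcome, and the outcome two weeks earlier predicting PTSD. Include time and the dependent variable's own two-week lag in each.
2. Put the variables on standardised scales. Hours of sleep, yes/no items and Likert items otherwise give paths that cannot be compared.
3. As a sensitivity analysis, replace the own lag with autoregressive residuals.
4. Conclude that improvement follows PTSD change only if the forward path is present and a direct comparison of the two standardised paths shows that it exceeds the reverse path. Otherwise report parallel change or association.

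The cost is a few extra models on diary data already collected as part of treatment. Two limits should be stated: a lagged outcome in a random-intercept model brings a modest bias, and protection is incomplete when diary items carry measurement error (18% and 43% false confirmation remained with the own lag in the two settings tried). If the extra models are not wanted, wording the result as an association is enough.

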#### Primary outcome: PTSD

2.6.1

The Life Events Checklist-5 (LEC-5) (37, 38) is a self-report measure that assesses type of trauma. It consists of 16 traumatic events that may lead to PTSD. The LEC-5 is administered a as part of regular diagnostics.

With the Clinician Administered PTSD Scale for DSM-5 (CAPS-5) (39, 40) we measure the presence and severity of PTSD. The CAPS-5 has a range of 0-80 with higher scores indicating more severe PTSD symptoms. In the last week of treatment the week-version of the CAPS-5 is standardly used at the treatment Centre to assess PTSD posttreatment (T2). The CAPS-5 has high interrater reliability (ICC = .98) and internal consistency (α = .90) for measuring PTSD severity. Based on considerations expressed by Larsen et al. (41) and Varker et al. (42), we define treatment response as a decrease of ≥9 points (11%) on the CAPS-5, remission as a CAPS-5 score of <12 and sustained PTSD remission at 6 and 12 months follow-up.

We use the PTSD Checklist for DSM-5 (PCL-5) (43) to assess the self-reported severity of PTSD. This questionnaire consists of 20 items with a 5-point Likert Scale (0-4) and has a range of 0-80. It is sensitive to measure change in PTSD symptoms and has good psychometric properties (43, 44).

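### The exploratory engagement analysis halves the sample on quantitative scores, which discards information, and its whole-course version measures engagement over the same weeks as the outcome

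*Protocol article*

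**What the plan says.** Section 3.1.2 of the protocol article (Symptom trajectories with diary data) takes as engagement measures "time spent on therapeutic assignments’ (in minutes) and ‘exposure assignments carried out’ (yes/no), as predictors of treatment outcome". The hypothesis is that clients who put more into treatment gain more from it. For the test, "we will split the sample in half to compare clients with the highest and lowest scores on homework and exposure assignments", with those scores taken "during the first four weeks and over the whole course of treatment". The halves are compared in linear mixed models with a time × group term.

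On outcomes: "We will use the CAPS-5 and PTSD symptoms of the diary to measure change in PTSD symptoms", and diary items on emotion dysregulation are used as well. Section 2.6.6 states that "clients keep a digital daily diary during the twelve weeks of treatment". Section 2.6.1 fixes the posttreatment interview (T2): "In the last week of treatment the week-version of the CAPS-5 is standardly used".

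Section 3.1.2 presents the diary work as exploratory. Section 2.2 defines the diary sample by start of treatment, from 2019 to December 2023, and gives no number.

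**The concern.** There are two separate problems.

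**Splitting.** Dividing the sample at the middle treats a client just above it as equal to the most active client, and as different in kind from a client just below it. The variation within each half is thrown away. The article gives no reason for the split, and the planned mixed model takes a continuous predictor equally well.

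**Timing.** Engagement over the whole course is not known until treatment ends, by which time the change it should predict has happened. Clients who feel better may do more assignments. Clients who leave early may fall in the low half if scores are totals. An association found this way could be created or inflated by improvement itself.

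At stake is an exploratory answer, not the primary result. Still, the Discussion (section 4) says the diary data will show whether investment in homework predicts results, and that statement would rest on this analysis.

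**Working it through.** **The plan's own sample size.** Section 2.8 gives N = 51 for a paired difference of 0.5 SD, alpha .01 and power .80. The noncentral t distribution, two-sided, reproduces 51 (power .809). Adding 10% gives 51 × 1.10 = 56.1, in line with the stated 56. This covers the paired t-tests only. The article gives no power for the engagement analysis.

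**Inputs for the split.** The documents give no correlation between engagement and change, no diary N, and no alpha specific to this analysis. Assumed: r = .3, .4, .5; N = 56 (the study total) and N = 100 for comparison; two-sided alpha .05 and .01; a normally distributed engagement score.

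**Formulas.** Splitting a normal predictor at its median multiplies its correlation with the outcome by √(2/π) = .798. The information kept is 2/π = .637, so about 36% is lost. Equal power needs about π/2 = 1.57 times as many clients. Power by Fisher z is Φ(atanh(r)·√(N − 3) − z), with z the two-sided critical value.

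**Worked case.** With r = .4, N = 56 and alpha .05:
- Continuous: .4236 × √53 − 1.96 = 1.12, power .87.
- Split: r = .4 × .798 = .319, atanh = .3307; .3307 × √53 − 1.96 = .45, power .67.

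**Power at N = 56:**

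| r | alpha .05, continuous | alpha .05, split | alpha .01, continuous | alpha .01, split |
|---|---|---|---|---|
| .3 | .62 | .43 | .37 | .21 |
| .4 | .87 | .67 | .69 | .43 |
| .5 | .98 | .87 | .92 | .69 |

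**Power at N = 100, alpha .05:** r = .3, .86 against .67 (19 points); r = .4, .99 against .90 (about 8 points before rounding).

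**N for 80% power at alpha .05, continuous against split:** 85 and 135 (r = .3); 47 and 75 (r = .4); 30 and 47 (r = .5).

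**Check in a change model.** With two time points, a predictor × time test is a regression of change on the predictor. A simulation (4,000 runs, n = 56, alpha .05) used a slope of .4 on change and an occasion-level residual SD of .7. The implied correlation is .4/√(.4² + 2 × .7²) = .37. Power was .82 with the continuous predictor and .61 with the split, the same order of loss.

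**Timing, set side by side:**

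| Version | Engagement window | Diary outcome window | T2 CAPS-5 |
|---|---|---|---|
| Whole course | weeks 1–12 | weeks 1–12 | week 12 |
| Early | weeks 1–4 | start not stated; diary runs weeks 1–12 | week 12 |

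In the whole-course version the diary windows coincide, and engagement runs up to the T2 interview. In the early version engagement precedes T2, but weeks 1–4 overlap with the diary outcome unless that series starts at week 5. Elsewhere in section 3.1.2 PTSD symptoms enter as a covariate lagged by two weeks, so the plan attends to temporal order there but does not carry it over to engagement.

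**The case against.** The best defence is that these analyses are labelled exploratory, that the early window is already planned and deals with much of the timing problem, and that the power figures rest on inputs the article does not supply. Most of this is fair. The diary sample is not tied to 56 and section 2.3 allows anonymized diary data from non-participants, so N may be larger. Minutes and counts need not be normal, so 36% is a reference value. The calculation is for a single correlation, not the full repeated-measures model. What remains is that the split is stated explicitly, has no stated advantage and costs information, and that the whole-course windows coincide.

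A reader might infer more than the article supports:

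- **BPD and cluster C scores are tested without a time interaction.** Section 3.1.1 says "We will include two predictors of treatment effects on PTSD severity" and does not list the model terms. It neither states nor excludes predictor × time, and an article may leave the equation to the full plan. The named time × group term in section 3.1.2 makes a clarification useful but does not show that the other is absent.
- **Yes/no outcomes go into linear models.** Section 2.6.6 says "Items vary from nominal, (yes/no), ordinal (5-point Likert scale) to continuous". The only item that section 3.1.2 marks as yes/no is a predictor, and aggregation of daily entries is not described.
- **Early leavers land in the low half by construction.** That needs total scores. The article does not say whether scores are totals or daily means.
- **Overlapping windows hide the effect.** Their consequence is bias and unclear direction; an association may just as well be inflated.

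**Conclusion.** The point holds for the engagement analysis only, in two parts.

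First, the split discards about 36% of the information if engagement is normally distributed. At an assumed N of 56 and r of .3 to .5, that is a loss of 11 to 20 points of power at alpha .05 and 16 to 26 points at alpha .01. The loss in points depends on N and r; it is reduced power, not inability to find an effect.

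Second, a whole-course association cannot be read as engagement predicting outcome, because both are measured over the same twelve weeks. The size of this bias cannot be calculated from the article. The early version is sounder but leaves the start of its diary outcome open.

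No primary conclusion is affected. The change is worth making because it is nearly free. The model terms for BPD and cluster C severity, and the handling of yes/no diary items, are matters to clarify and are not counted as defects.

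**What to change.** - Enter mean daily homework minutes and the proportion of days with an exposure assignment, both over weeks 1–4, as continuous predictors with a predictor × time term.
- Use them to predict diary change from week 5 on, and CAPS-5 change. CAPS-5 change from T1 to T2 still spans weeks 1–4, so the diary series from week 5 gives the cleaner ordering in time.
- Label whole-course engagement as descriptive.
- Keep the two halves for plots only.

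Daily means and proportions also stop early leavers from scoring low merely because they have fewer diary days. The cost is a few sentences in the plan and a small change to model code. No new data are needed.
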